### Qualitative study

Qualitative research methods will be used in order to explore aspects of the interventions and women's experiences of the decision making in more depth. Specifically, semi-structured interviews will be conducted with a sample of women from each of the intervention arms (Decision Analysis and Information), across the research sites in Bristol and Dundee. These interviews will explore:

(1) Women's views and experiences of the intervention and its delivery – for example, the quality and relevance of the decision aid/information, what they felt about the risk information presented to them, and which particular aspects of each intervention were helpful or unhelpful.

(2) Which factors women felt had most influenced their preferences regarding method of delivery.

(3) Whether the women had prior preferences about method of delivery, whether/how these changed during their pregnancy and in the case of the decision analysis, what they felt about the method of delivery proposed by the intervention compared to any prior preferences.

(4) Any other information sources women sought and used to help them make a decision about method of delivery (for example, information from health professionals, partner/family/friends, internet, media, books).

(5) Women's views and feelings about their actual method of delivery compared with any prior preferences and the method of delivery suggested by the intervention (for decision analysis).

A small number of interviews may also be conducted with women in the usual care arm of the trial to explore what support and advice was normally provided during pregnancy to those who did not receive an intervention.

A sample of approximately 30 women across the two intervention arms will be interviewed in depth to ensure a thorough exploration of emergent themes and concepts. Within each arm, women will be purposefully chosen to include those with different parities/ages/socio-economic backgrounds, and where possible different methods of delivery/outcomes, following a maximum variation sampling strategy [31]. The interviews will take place a short time after the primary follow up, to avoid any influence of the interview on these measures. A subset of the women will be interviewed a second time six to eight weeks after birth in order that they can reflect upon their decision regarding preferred mode of delivery with the actual mode of delivery. In addition, a small number of interviews may take place closer in time to receipt of the intervention if this is deemed (a) feasible given recruitment and (b) worthwhile in terms of providing new information to that gleaned from qualitative interviews undertaken in the development phase of the trial.

Interviews will be conducted in the womens' homes or other suitable setting chosen by them. A check-list of topics will be used to ensure that the primary issues are covered, whilst allowing flexibility for new issues to emerge from each interview. Interviews will be recorded on mini-disc, fully transcribed and anonymised to protect confidentiality. Transcripts will be studied in detail and a list of common themes and concepts drawn up. Data collection and analysis will run in parallel and the coding index added to or refined and coded material regrouped as new themes and categories emerge from subsequent interviews [32]. Further analysis will employ the constant comparison method of grounded theory in which the textual data is scrutinised for differences and similarities within themes keeping in mind the context in which mention of these themes arose in each interview [32].

In addition to the interviews with women, a small number of focus groups with health professionals (e.g. obstetricians, midwives) in each research site may be conducted near the end of the trial, resources and time permitting. Focus groups are often used in evaluations of new services/interventions and are useful for exploring group views, concerns and preferences (e.g. consensus or disagreement about an issue) [33]. They may be valuable for exploring professionals' views about the intervention and issues around implementation into routine practice.

### Economic evaluation

The aim of the economic evaluation is to compare the costs and benefits of the two interventions with usual care. The analysis will be from an NHS perspective and will be based on the costs incurred during pregnancy, delivery and 6–8 weeks following delivery. Incremental cost effectiveness ratios will be formed comparing (i) the cost per point improvement on the Decisional Conflict Scale (DCS) and (ii) the cost per extra patient able to make a decision (represented by a 0.5 standard deviation change on the DCS). We will also compare the average cost of care per patient in each arm of the trial with patient satisfaction. Differences in the cost of care of women receiving the two interventions will be compared with usual care from the point at which patients are randomised. The analysis will include all resources under the control of the NHS that may differ as a result of the interventions and will include resources used by both mother and baby. The costs identified as being of relevance are: antenatal appointments in addition to routine appointments, including both primary and secondary care; mode of delivery and related hospital stay for mother and baby; follow up care for mother and baby, including primary and secondary care appointments, outpatient appointments, inpatient stays, A&E visits, and prescribed medication.

Data on resource use will be collected principally by two questionnaires completed by the women. The first questionnaire, completed at 36–37 weeks' gestation, will provide information on all antenatal appointments, and the proportion of these that involved discussion about mode of delivery. Women will be asked how often mode of delivery was addressed at (i) routine appointments, and (ii) appointments initiated by them to discuss mode of delivery. A sample of 10 hand-held records from each arm at each main centre (St Michaels, Southmead and Ninewells, total 90) will be scrutinised to validate the information given in response to the questionnaire. The second questionnaire, completed six to eight weeks after delivery, will provide information on mode of delivery and all non-routine postnatal health service contacts and prescriptions for both mother and baby.

The principle of opportunity cost will underlie the valuation of resource use. In many cases, market rates will act as a proxy for opportunity cost. National data sets such as the Unit Costs of Health and Social Care [34] and the British National Formulary [35] will be used to value primary care consultations and prescribed medication. Secondary care contacts will be coded according to Healthcare Resource Group (HRG) and valued using the Department of Health National Reference Costs [36].

Costs and outcomes will not be discounted, as the economic evaluation will be limited to a period of 12 months. Sensitivity analysis will be conducted in areas where there is uncertainty around assumptions about resource use measurement and/or valuation. Variation in resource use and the effectiveness of the intervention is not captured by a cost-effectiveness/utility ratio. We will use bootstrapping to address this, and construct a cost effectiveness acceptability curve.

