## Aim

The aim of this paper is to describe the protocol for a randomised controlled trial of two interventions to aid decision making about mode of delivery among pregnant women with one previous CS. The interventions being assessed are (1) Decision analysis, and (2) Information programme and website. Both decision aids will be compared with usual care given by the obstetric team. The interventions will be assessed in terms of decisional conflict, planned and actual mode of delivery, anxiety, knowledge, perception of shared decision making and satisfaction with the decision making process. Development and piloting of the interventions took place in 2003–2004, and the main phase of the study started in May 2004 and will continue until December 2006. Ethical approval for the study was obtained from the UK South West Multi-Centre Research Ethics Committee.

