### Outcome measures

There are two primary outcomes:

(1) Decisional Conflict Scale (DCS) [28,29]. This is a 16 item questionnaire that measures degree of uncertainty about which course of action to take and the main modifiable factors contributing to uncertainty. Previous research indicates that effect sizes of about 0.35 to 0.5 standard deviations can discriminate between individuals who make a decision and those who delay or are unsure [28]. Assuming a standard deviation of 15 points [18], this is equivalent to differences of 5.25 to 7.5 points on the total DCS 100 point scale.

(2) Actual mode of delivery (vaginal, elective CS, or emergency CS). Unlike a previous trial [20], we are not seeking to promote one method of delivery over another. However differences between the arms in the proportions of different modes of delivery may have important healthcare resource implications.

There are five secondary outcomes: anxiety; [30] knowledge; perception of shared decision making; satisfaction with decision making process; proportion of women attempting vaginal delivery.

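### The economic evaluation's second ratio does not measure cost per extra woman able to decide, because a between-group effect size stands in for deciding

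*Protocol article*

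**What the plan says.** The protocol's Economic evaluation section plans two incremental cost-effectiveness ratios. The first is "the cost per point improvement on the Decisional Conflict Scale (DCS"). The second is "the cost per extra patient able to make a decision (represented by a 0.5 standard deviation change on the DCS").

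The 0.5 SD comes from Outcome measures, which reports earlier research on the scale: "effect sizes of about 0.35 to 0.5 standard deviations can discriminate between individuals who make a decision and those who delay or are unsure". That section continues "Assuming a standard deviation of 15 points" and concludes that "this is equivalent to differences of 5.25 to 7.5 points on the total DCS 100 point scale".

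On comparators, the economic section opens: "The aim of the economic evaluation is to compare the costs and benefits of the two interventions with usual care". It later sets cost differences against usual care again. Statistical analysis, by contrast, plans all three pair-wise comparisons for both primary outcomes.

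The sensitivity analysis described for the economic evaluation concerns how resource use is measured and valued. It does not mention the 0.5 SD definition.

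**The concern.** An effect size that separates two groups on average is not a threshold that tells whether one person has decided. A woman with low conflict at baseline may already have decided and have little room to improve. A woman with high conflict may improve by 0.5 SD and still be undecided. The second ratio nevertheless carries a label that an NHS decision maker would take as a count of women helped to a decision.

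The text also leaves open whether the change is counted woman by woman or applied to the difference between arm means. The two give very different denominators from the same data, and no stated sensitivity analysis would show it.

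A related point is the comparator. If both aids work, a reader needs to know whether the dearer one is worth its extra cost over the other. The economic section is framed only against usual care.

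**Working it through.** **Inputs.** From the protocol: DCS standard deviation 15; effect sizes 0.35 and 0.5 SD; DCS measured at baseline and after the 36–37 week visit; 600 women in three arms, two-sided alpha 1%. Assumed, because the protocol does not give them: 200 women per arm, normal scores, equal SD at both times, and a baseline to follow-up correlation r of 0.3 to 0.7 (0.8 and 0.9 also shown).

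**Step 1: the plan's own figures.** 0.35 × 15 = 5.25 points and 0.5 × 15 = 7.5 points, as stated. Power for a between-group difference d is Φ(d√(200/2) − 2.576). At d = 0.35 this is Φ(0.924) = 82.2%; at d = 0.5 it is Φ(2.424) = 99.2%. The stated range is 82–99%. The sample size section therefore uses the 0.35–0.5 SD as a difference between groups.

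**Step 2: arm-mean reading.** Let C be the incremental cost per woman and D the difference in mean DCS improvement, in points. Ratio (i) is C/D. If each 7.5 points counts as one extra decider, ratio (ii) is C/(D/7.5) = 7.5 × C/D, that is, ratio (i) multiplied by a constant. It can also give impossible counts: a 0.7 SD difference would mean 0.7/0.5 = 1.4 extra deciders per woman.

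**Step 3: per-woman reading.** The SD of change is 15√(2(1 − r)). With a true mean improvement of s points, the proportion improving by at least 7.5 points is 1 − Φ((7.5 − s)/SD of change). For s = 7.5 this is 50% at any r. For s = 0 (usual care) it depends on r:

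| r | SD of change | Usual care, s = 0 | Intervention, s = 7.5 | Difference |
|---|---|---|---|---|
| 0.3 | 17.7 | 0.336 | 0.500 | 0.164 |
| 0.5 | 15.0 | 0.309 | 0.500 | 0.191 |
| 0.7 | 11.6 | 0.259 | 0.500 | 0.241 |
| 0.8 | 9.5 | 0.215 | 0.500 | 0.285 |
| 0.9 | 6.7 | 0.132 | 0.500 | 0.368 |

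**Step 4: the two readings compared.** For the same true 0.5 SD benefit, the arm-mean reading gives 0.5/0.5 = 1.0 extra decider per woman. The per-woman reading gives 0.164 to 0.241 for r from 0.3 to 0.7. The cost per extra decider is then C under the first reading, and between C/0.241 (about 4C) and C/0.164 (about 6C) under the second. The gap narrows to 1/0.368, about 2.7-fold, at r = 0.9. A true 0.35 SD benefit behaves similarly: 0.35/0.5 = 0.7 against 0.114 to 0.164, again about four- to sixfold.

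**The case against.** Several stronger readings are tempting, and the documents do not support them.

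- *Many women would be misclassified.* This needs a per-woman threshold, which the wording suggests but does not fix. Under the arm-mean reading no woman is classified at all.
- *A quarter to a third of women would be falsely counted as extra deciders.* The 26–34% who cross 7.5 points with no true mean change (13% at r = 0.9) occur in every arm. The denominator is a difference between arms, so with no treatment effect this chance crossing cancels in expectation.
- *Two groups 0.5 SD apart can be told apart only about 60% of the time.* That is true of the best cut-off on a single score, for normal, equally common groups. The plan uses a change, not such a cut-off, so the figure does not measure this analysis.
- *The ratio is meaningless.* It can be read as a cost per woman improving by 7.5 points, or as the first ratio on another scale.
- *Ratios against usual care cannot choose between the aids.* The sentence defining the ratios names no comparator, cost per arm is to be set beside satisfaction, an acceptability curve is planned, and the head-to-head contrast can be derived by subtraction.

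It is also fair that a condensed article may leave the operational definition to a fuller document, and that the cited source for the effect size cannot be checked here. What survives is narrower: the article does state what the second denominator represents, and the effect size it relies on does not justify that label under either reading.

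**Conclusion.** The point holds as one of labelling and definition. The second ratio is either the cost per extra woman improving by at least 7.5 points or a multiple of the first ratio. In neither case is it the cost per extra woman able to decide. That conclusion follows from the text alone. The four- to sixfold gap between the readings rests on normal scores, equal SD at both visits, no mean change under usual care and a correlation of 0.3–0.7; it is smaller at higher correlations. The factor of 7.5 rests on the assumed SD of 15.

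The economic comparison is also framed more narrowly than the three pair-wise effectiveness comparisons. The article does not rule out a full incremental analysis, so this is an improvement to make rather than an error that invalidates the evaluation.

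The consequence is minor for the trial as a whole: the first ratio, both primary outcomes and the sample size are untouched.

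**What to change.** - Stop describing the second ratio in terms of women able to decide. Either drop it or report it as the cost per extra woman improving by at least 0.5 SD (7.5 points) from baseline to 36–37 weeks, taken as a difference between arms.
- Vary the threshold in sensitivity analysis, for example 5.25 and 7.5 points.
- If the preference data already collected include an undecided category, the proportion with a definite planned mode could be added as a supplementary denominator; the Aim lists "planned and actual mode of delivery" among the assessments. Note that this proportion may be near its ceiling after the 36–37 week visit, whose purpose is to settle the plan. That would make the ratio unstable, so it should not be the main denominator. Adding a new response option now would change a questionnaire in a running trial and is not proposed.
- Replace the comparison against usual care alone with a full incremental analysis of the three arms (order by cost, remove dominated options) and a three-option acceptability curve, in line with the pair-wise comparisons in Statistical analysis.

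The cost is a little more analysis and a less appealing label. No new data are needed.

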**Methods/design:**

Women with one previous CS are recruited to the trial during their booking visit at approximately 12–20 weeks' gestation in participating maternity units in Bristol, Weston and Dundee. Using central randomisation, women are allocated to one of three arms: information programme and website; decision analysis; usual care. Both interventions are computer-based, and are designed to provide women with detailed information about the potential outcomes for both mother and baby of planned vaginal delivery, planned CS and emergency CS. The decision analysis intervention additionally provides a recommended 'preferred option' based on maximised expected utility. There are two primary outcomes (decisional conflict and actual mode of delivery), and five secondary outcomes (anxiety, knowledge, perceptions of shared decision making; satisfaction with decision making process, proportion of women attempting vaginal delivery). Primary follow up for the questionnaire measures is at 36–37 weeks' gestation, and a total of 660 women will be recruited to the study. The primary intention-to-treat analyses will comprise three pair-wise comparisons between decision analysis, information and usual care groups, for each of the two primary outcomes. A qualitative study will investigate women's experiences of the decision making in more depth, and an economic evaluation from the perspective of the NHS will be conducted.

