### Statistical analysis

Data analysis will proceed according to CONSORT guidelines for randomised controlled trials. The first stage of the analysis will be to use descriptive statistics to describe the group of individuals recruited to the trial in relation to those eligible, and to investigate comparability of the trial arms at baseline. The primary analyses will comprise three pair-wise intention-to-treat comparisons between decision analysis, information and usual care groups, for each of the two primary outcomes. These comparisons will use appropriate (that is, standard or logistic) multivariable regression models, adjusting for maternity unit, initial preference regarding mode of delivery, and value of the outcome variable at baseline. Full attention will be paid to the estimates and confidence intervals for these comparisons as well as the p-values, with the latter adjusted for multiple comparisons using Tukey's procedure. Secondary outcomes will then be analysed in the same way, using appropriate multivariable regression models depending on the nature of the outcomes.

Other secondary analyses will involve investigation of the short-term effects of the interventions using data from the two week follow up, and the effects at 36–37' weeks gestation adjusted for both baseline and two week follow up. Pre-planned subgroup analyses employing appropriate interaction terms in the regression models will be used to ascertain any differential effects of the interventions on the two primary outcomes across the following categories of women: previous caesarean section occurring before or after labour; previous successful vaginal delivery; stated preferred mode of delivery. Since the trial is powered to detect overall differences between the groups rather than interactions of this kind, the results of these essentially exploratory analyses will be presented using confidence intervals as well as p-values, and interpreted with due caution. Finally, we will investigate the effect of differential use of the information intervention via the internet using descriptive statistics and appropriate comparisons with the other groups.

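### The economic evaluation names usual care as its comparator and states no comparison between the two decision aids, so an aid that is poor value beside the other could still look acceptable

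*Protocol article*

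**What the plan says.** All references are to the protocol article. Its abstract describes three alternatives: "women are allocated to one of three arms: information programme and website; decision analysis; usual care".

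The Economic evaluation section opens with "The aim of the economic evaluation is to compare the costs and benefits of the two interventions with usual care". On costs it then says "Differences in the cost of care of women receiving the two interventions will be compared with usual care", counting from randomisation.

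Three other sentences in that section bear on the point:

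- **Ratios:** "Incremental cost effectiveness ratios will be formed comparing (i) the cost per point improvement on the Decisional Conflict Scale (DCS"), followed by (ii) a ratio per extra woman able to decide. Neither names a comparator.
- **Satisfaction:** "We will also compare the average cost of care per patient in each arm of the trial with patient satisfaction". This covers all three arms but is not an incremental ranking.
- **Uncertainty:** "We will use bootstrapping to address this, and construct a cost effectiveness acceptability curve". The options to appear on the curve are not given.

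The Statistical analysis section, by contrast, plans "three pair-wise intention-to-treat comparisons between decision analysis, information and usual care groups" for each primary outcome.

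**The concern.** A health service can provide the information programme, the decision analysis, or neither. Among mutually exclusive options, the relevant ratio for each one is its extra cost over its extra effect relative to the next less costly option still in contention. A ratio against usual care merges two steps, from usual care to the cheaper aid and from the cheaper aid to the dearer one. A cheap and effective first step can then conceal a very expensive second step.

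Usual care is the only comparator that the economic section names. If the ratios and the curve are built on that comparator, both aids may pass at the same threshold, and the analysis would not say which to provide. The Discussion says the trial aims to inform best practice by evaluating both aids, so that choice matters. The economic conclusion is at stake; the clinical analyses are not.

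**Working it through.** **Inputs.** The article gives no intervention costs and no threshold per point on the Decisional Conflict Scale (DCS), so there is no stated figure to reproduce for this point. The costs, and the effects in the first illustration, are assumed. The only scale available is the DCS difference under Outcome measures: 0.35 × 15 = 5.25 to 0.5 × 15 = 7.5 points, which agrees with the stated range.

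**Formulas.** Let C and E be extra mean cost and DCS improvement relative to usual care, which is (0, 0).

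- Ratio against usual care = C / E.
- Ratio between the aids = (C_decision − C_information) / (E_decision − E_information).
- Net benefit at threshold λ = λ × E − C. The best option is the one with the highest value.

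**First illustration.** Information (20, 4); decision analysis (60, 5).

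- Against usual care: 20/4 = 5 and 60/5 = 12 per point.
- Between the aids: (60 − 20)/(5 − 4) = 40 per point.
- At λ = 15: usual care 0; information 15 × 4 − 20 = 40; decision analysis 15 × 5 − 60 = 15.
- At λ = 40: information 40 × 4 − 20 = 140; decision analysis 40 × 5 − 60 = 140, the point of indifference.

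Usual care is best below 5, information from 5 to 40, and decision analysis above 40. Between 12 and 40, decision analysis passes against usual care although information is the better choice.

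**Three further cases, costs again assumed.** Some of the effects lie at or near the article's DCS range; others are set below it to produce the pattern in question.

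| Case | Information (C, E) | Decision analysis (C, E) | Information vs usual care | Decision analysis vs usual care | Decision analysis vs information |
|---|---|---|---|---|---|
| A | 20, 5.25 | 90, 6.0 | 3.8 | 15.0 | 70/0.75 = 93.3 |
| B | 20, 5.25 | 90, 5.0 | 3.8 | 18.0 | costs 70 more, 0.25 points less benefit |
| C | 60, 3.0 | 90, 7.5 | 20.0 | 12.0 | 30/4.5 = 6.7 |

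In case A, decision analysis passes against usual care but not against information at thresholds from 15 to about 93. In case B it shows 18.0 per point against usual care while information dominates it. In case C information is extendedly dominated: its 20.0 per point exceeds the 6.7 for the next step up, yet at any threshold above 20 it would pass against usual care.

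**Carry-over to the curve.** At λ = 15 in the first illustration both aids have positive net benefit, so two separate curves against usual care would each tend to favour their aid. Those two probabilities are not probabilities of being the best of three and do not rank the aids.

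**The case against.** A reader might infer that the article restricts the economic analysis to usual care only. The text does not support that. The sentences on ratios and on the curve leave the comparator open, and nothing rules out a comparison of the two aids. The Aim section also speaks of comparing both aids with usual care, yet the Statistical analysis section goes on to plan all three pairs. In this article such wording is therefore not necessarily exclusive. The sentence on cost differences also serves to fix when costing starts. A single curve covering three options would fit the text, and separate curves against usual care are nowhere described.

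A reader might also infer that the plan cannot reveal dominance. That is too strong. If cost and effect differences against usual care are reported for both aids, the contrast between the aids follows by subtraction, as in the working above, and the head-to-head DCS comparison is already planned.

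Finally, an article may leave dominance rules and curve layout to a fuller plan, and every cost used here is assumed.

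These points narrow the concern but do not remove it. Usual care is named as comparator twice, in the governing aim and for costs, and the economic section states no comparison between the aids. What it states is incomplete, which differs from leaving detail unsaid. Subtraction recovers point estimates from cost and effect differences, but not from the two ratios alone. Nor does it give the uncertainty of the contrast: the two usual-care comparisons share an arm, so that uncertainty must come from resampling the arms together.

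**Conclusion.** The point holds in a limited form. The stated economic comparator is incomplete for a three-arm choice and is out of step with the three pair-wise comparisons planned for the primary outcomes. If the ratios and curve follow the stated aim, a dominated or poor-value aid can look acceptable. In the first illustration, decision analysis does so at thresholds from 12 to 40 per point.

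This conclusion assumes that the aids are mutually exclusive options for the service and that the open sentences are read in line with the section's aim. The figures show that the problem can arise; they do not show that it will, or how large it would be in this trial, because the costs and threshold are unknown. The primary clinical analyses and the sample size are unaffected. This is an inexpensive improvement to the economic section.

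**What to change.** In the Economic evaluation section, extend the aim and the cost-difference sentence to cover all three arms, and state a full incremental analysis:

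1. Order the arms by mean cost.
2. Remove dominated and extendedly dominated options.
3. Form each ratio against the next less costly remaining option.
4. Bootstrap the three arms together, keeping each woman's cost and effect paired.
5. Plot acceptability curves that give, at each threshold, each arm's probability of having the highest net benefit.

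The cost is some rewording and a little more analysis. Cost and DCS data are already to be collected in every arm, so no new data or participants are needed. Settling the comparator beforehand also prevents it being chosen once results are known.
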